### Settings and eligibility

The study population encompasses subjects diagnosed with non-infectious intermediate, posterior or panuveitis with active disease within 180 days before the start of the study (baseline visit), and either a documented failure to systemic or local GCs, or a chronic disease requiring GC-sparing ISD treatment. Main inclusion and exclusion criteria can be found in table 2.

**Table 2 T2:** Study participant inclusion and exclusion criteria

Inclusion criteria	Exclusion criteria
Adult subjects (≥18 years old)	Subjects with ocular histoplasmosis syndrome, or ocular masquerade syndromes
Diagnosed with non-infectious intermediate, posterior or panuveitis in at least one eye	Evidence or history of malignancy
Who have active disease within the previous 180 days before baseline, and either	Corneal, lens or vitreous opacities precluding the visualisation of the fundus
A documented failure to systemic or local GCs in the previous 6 months, OR	Uncontrolled intraocular pressure
A chronic disease necessitating GC-sparing immunosuppressive treatment (such as multifocal choroiditis with panuveitis, serpiginous choroidopathy, birdshot retinochoroidopathy, diffuse retinal vasculitis, Vogt-Koyanagi-Harada with bullous serous retinal and/or choroidal detachments or sympathetic ophthalmia)	Best-corrected visual acuity (CVA) <20/400
Able and willing to self-administer subcutaneous (SC) injections or have a qualified person available to administer SC injections	History, symptoms and/or MRI findings suggestive of a demyelinating disease
A negative PPD test (or equivalent) and a chest X-ray (CXR) at Screening OR if positive PPD test (or equivalent) and/or a CXR consistent with prior tuberculosis (TB) exposure, the subject must initiate, be currently receiving or have documented completion of a course of TB prophylaxis therapy, according to clinical practice	History of moderate to severe congestive heart failure (NYHA class III or IV)
	Behçet’s disease or suspected of Behçet’s disease
	Previous exposure to TNFi therapies
	Previous exposure to synthetic ISDs in the previous 6 months before baseline
	Prior intolerability, safety issues or ineffectiveness of MTX and/or ADA
	Use of GCs implants (Iluvien within 3 years, Ozurdex within 6 months before baseline)
	Use of intraocular or periocular GCs injection within 90 days before baseline
	Ocular surgery within 30 days before baseline
	Planned (elective) eye surgery in the following 52 weeks from baseline
	Proliferative or severe non-proliferative diabetic retinopathy
	Neovascular/wet age-related macular degeneration
	Chronic structural damage considered by the Investigator to interfere with measurement of macular thickness, impede the potential for its normalisation or can cause damage independent of the inflammatory process
	Systemic inflammatory disease considered by the Investigator as likely to require high GCs dosage or prohibited medications
	Presence of chronic recurring infections (HBV, syphilis), active TB and/or a history of invasive infection
	Positive pregnancy test
	Breast-feeding or considering becoming pregnant during the study

ADA, adalimumab; GC, glucocorticoids; ISDs, immunosuppressive drugs; MTX, methotrexate.

Subjects will be recruited from 16 Spanish academic hospitals located in different regions of Spain (Galicia, País Vasco, Castilla y León, Comunidad de Madrid, Castilla La Mancha, Comunidad Valenciana and Comunidad Canaria). In addition, the Instituto de Investigación Biomédica de A Coruña (INIBIC) will carry out the proteomic analysis, and the Instituto de Investigación Sanitaria San Carlos (IdISSC) Musculoskeletal Pathology Group will be responsible for the pharmacogenetic analysis and development of prediction models for drug response.

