Regarding adalimumab (ADA), its effectiveness in NIU has been shown in two randomised controlled trials.^28 29^ The VISUAL I study^28^ compared ADA with placebo in 217 NIU patients with active uveitis despite ≥10 mg/day of systemic GCs. Based on the cumulative number of subjects with treatment failure in each visit, by week 25 (about 6 months), 31 of 107 (29%) subjects in the placebo group and 62 of 110 (56%) subjects in the ADA group had not suffered a treatment failure. By 50 weeks, the numbers were reduced to 24 (22%) and 51 (46%), respectively. Regarding safety, many of the AEs are sufficiently mild to not require discontinuation, such as injection site pain and antidrug antibodies formation,^19 30 31^ reflecting in a high retention rate.^32^ Regarding SAEs, there was no association with higher risk in a recent meta-analysis,^33^ compared with placebo or synthetic ISDs. However, ADA was associated with a higher risk of treatment discontinuation due to SAEs. One of the most important ADA’s AEs are infections. However, a previous meta-analysis reported that the absolute risk was low (0.036% with TNF-alpha inhibitors vs 0.017% with placebo),^34^ which probably does not represent a clinically important constraint on the use of these agents. Finally, ADA has not showed an association with a higher risk of malignancy.^33^

Although ISDs are usually used in monotherapy in uveitis, several observational studies have shown that in 21%–52% of NIU patients, the use of ISDs in monotherapy was unable to achieve a sustained control of the inflammatory process.^27 35–37^ Furthermore, other studies have provided evidence that the combination of two or more ISDs could offer advantages in terms of effectiveness and tolerability,^38–41^ in conditions such as Birdshot retinochoroidopathy,^38^ serpiginous choroiditis,^39 40^ Vogt-Koyanagi-Harada syndrome (VHK),^42 43^ ocular Behçet’s disease,^44 45^ JIA associated uveitis,^46^ sympathetic ophthalmia^47^ and intermediate uveitis.^48^ Regarding the beneficial of combining both MTX and ADA, several RCTs have provided evidence in other immune-mediated inflammatory diseases (IMIDs).^49^ In NIU, this combination was tested in children with Juvenile Idiopathic Arthritis-associated Uveitis and a previous failure to MTX monotherapy.^50^ The combination of MTX and ADA was more effective compared with MTX and placebo, although it was associated with a higher proportion of AEs (88% vs 83% of patients) and SAEs (22% vs 7%).

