### Objectives and outcome variables

The trial main hypothesis is that the use of combination therapy with MTX and ADA will be more effective in inducing and maintaining ocular inflammatory inactivity than either drug given in monotherapy.

The *primary efficacy objective* is to establish which treatment strategy results in a higher proportion of subjects achieving a complete and maintained resolution of the ocular inflammation, on an intent to treat basis. The *primary efficacy outcome* will be the proportion of patients achieving a *Good Clinical Response* between the combination therapy arm and the single ISD arms. This outcome is defined as a complete resolution of the ocular inflammatory signs (including active chorioretinal lesions, active retinal vascular inflammation, uveitis macular oedema, presence of anterior chamber cells and presence of vitreous haze), achieved within the first 16 weeks of the study and maintained during follow-up until the end of the study (week 52); furthermore, there must not be a treatment failure due to safety or intolerability; the subject must adhere to the initial (up to week 16) oral GCs tapering protocol; all study visits from baseline to 16 weeks must be completed and at the final visit (week 52), the subject must be treated with up to 7.5 mg/day of oral prednisone (or equivalent) and up to two times a day of prednisolone acetate 1% (or equivalent). The *secondary efficacy objectives* and outcomes variables can be found at table 1.

**Table 1 T1:** Efficacy-related secondary objectives and outcome variables

Objective	Outcome variable
To compare the fraction of subjects who achieve a complete inflammatory ocular inactivity by week 16	Complete abrogation of the ocular inflammatory signs, which is achieved within the first 16 weeks of the study, no treatment failure due to safety or intolerability; compliance with the initial (up to week 16) oral GCs tapering protocol, and completion of all study visits from baseline to 16 weeks
To compare several Patient-Reported Outcomes Measures (health-related and vision-related quality of life, anxiety and depression) between treatment strategies	EuroQuol 5D-5L Visual Functioning Questionnaire-25 Hospital Anxiety and Depression Scale

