### Recruitment

It will extend over 18 months. The participating study sites attends several 10s of new patients every year, with several hundreds or thousands being followed-up, and many of these sites act as reference centres for other secondary and tertiary hospitals. Candidate subjects will be identified from patients lists AND/OR research databases AND among the new patients attended at the sites.

Subject will not receive any financial compensation for participating in the study.

To ensure subject’s retention during follow-up, we will request contact details, carry out reminder phone calls/send emails, review barriers to attend appointments, and educate them in the significance of research follow-up even if they decide to discontinue the study drugs.

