### Intervention

All subjects entering the study will be centrally randomised at the baseline visit into one of three study arms, in a 1:1:1 ratio:

*Arm 1* will receive at the baseline visit ADA 80 mg SC loading dose followed a week later by 40 mg every-other-week starting at week 1. They will also receive MTX oral at the baseline visit, with initial dose of 15 mg/week, increasing up to 25 mg/week.

*Arm 2*: MTX with the same schedule as in arm 1.

*Arm 3*: ADA with the same schedule as in arm 1.

In addition to the study drugs, topical adjunctive eye medication will be allowed according to standard practice (intraocular pressure-lowering medication, cycloplegic agents, artificial tears, topical non-steroidal anti-inflammatory drugs…). The use of any biologic therapies with a potential therapeutic impact in NIUs, live vaccines, any other ISD besides the study drugs, intraocular GCs implants or intraocular surgery will be prohibited for the duration of the trial.

To ensure a balance of patients across treatment groups and uveitis anatomic locations, patients will be stratified according to the main site of ocular inflammation (intermediate, OR posterior/panuveitis). Randomisation will not be stratified by site due to the small-expected number of subjects per site.

Block randomisation will ensure that an equal number of patients are randomised to each study arm.

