Intervention(s)	Intervention 1: Adalimumab 40 mg every-other-week (plus a 80 mg SC loading dose)+methotrexate oral, up to 25 mg/week, both for a duration of 52 weeks
	Intervention 2: Methotrexate with the same schedule as in intervention 1
	Intervention 3: Adalimumab with the same schedule as in intervention 1
Key inclusion and exclusion criteria	Age≥18 years old Diagnosed with non-infectious intermediate, posterior or panuveitis in at least one eye Active ocular disease Lack of satisfactory response to systemic and/or local glucocorticoid (GC) therapy AND/OR diagnoses of a chronic disease usually necessitating GC-sparing immunosuppressive treatment
Study type	Phase III, multicentre, prospective, randomised, single-blinded with masked outcome assessment, parallel three arms with 1:1:1 allocation, active-controlled, superiority study design
Date of first enrolment	N/A
Target sample size	64 per treatment arm (192 in total)
Recruitment status	Not yet recruiting
Primary outcome	Complete resolution of the ocular inflammatory signs, which is achieved within the first 16 weeks of the study, and maintained during follow-up until the end of the study (week 52)
Key secondary outcomes	Safety, cost-effectiveness

N/A, not applicable.

Data obtained through this study may be provided to qualified researchers with academic interest in uveitis. Data or samples shared will be coded, and donated to a Registered Biobank and made available under legal requirement. Approval of the request and execution of all applicable agreements are prerequisites to the sharing of data with the requesting party.

Regarding dissemination, in order to communicate the clinical trial progress and findings to a broad group of stakeholders, we will elaborate a dissemination plan which will include production of materials adapted to scientific meetings, scientific publications, patients and other stakeholders. A summary of the final version of the study protocol will be made available through the Spanish Clinical Trial Registry and Clinicaltrials.gov database. The promoter will be the only with access to the participant-level data, following the regulation on data protection.

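### The 180-day activity window lets subjects quiet at baseline enter, Table 5 words the criterion differently, and baseline activity is not a stratum of the primary test

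*Protocol article*

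**What the plan says.** In the protocol article, Settings and eligibility gives the activity requirement twice. The text describes subjects "with active disease within 180 days before the start of the study (baseline visit"), and Table 2 says "Who have active disease within the previous 180 days before baseline, and either", followed by two routes: recent glucocorticoid failure, or chronic disease needing a glucocorticoid-sparing drug. No criterion shown asks for inflammation at the baseline exam. Table 5, under Ethics and dissemination, lists the key criterion as "Active ocular disease".

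The main hypothesis is that the combination is "more effective in inducing and maintaining ocular inflammatory inactivity than either drug given in monotherapy". The primary outcome, Good Clinical Response, needs complete resolution of the listed inflammatory signs "achieved within the first 16 weeks of the study and maintained during follow-up until the end of the study (week 52"). It also needs adherence to the taper and all visits to week 16, no failure for safety or intolerability, and limits on oral and topical glucocorticoid at week 52.

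The primary test compares the combination with both monotherapy arms together, in all randomised subjects, each counted as achieving the outcome or not. At randomisation "patients will be stratified according to the main site of ocular inflammation (intermediate, OR posterior/panuveitis"), and the Mantel-Haenszel test uses the same two strata.

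**The concern.** A subject who flared five months ago and has no inflammatory sign at baseline fits Table 2. Entry of such subjects is realistic: "Candidate subjects will be identified from patients lists AND/OR research databases AND among the new patients attended at the sites", and the Recruitment section says sites follow hundreds or thousands of patients. Such a subject has nothing to resolve. The primary response rate then mixes two tasks: induction plus maintenance for those active at entry, and maintenance alone for those quiet at entry.

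The planning figures lean towards active disease. The Introduction describes the adalimumab source trial as enrolling patients with "active uveitis despite ≥10 mg/day of systemic GCs", and the 43% monotherapy rate is built as attainment at 6 months followed by losses.

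Three things are at stake. The week-16 comparison is the most exposed, because it has no long maintenance period. A factor likely to predict the outcome strongly is left out of the primary test. And a reader of the summary table would picture a different population from the one that Table 2 admits.

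**Working it through.** **1. The plan's own sample size.** Inputs from Sample size determination: 43% on monotherapy, a gain of 23 points (66%), power 80%, significance level 0.05 (taken as two-sided). From the primary analysis: one arm against two pooled, so r = 2.

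n = [1.96·√((1+1/r)·p̄(1−p̄)) + 0.842·√(p₁(1−p₁) + p₂(1−p₂)/r)]² / (p₁−p₂)²

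With p₁ = 0.66, p₂ = 0.43 and p̄ = (0.66 + 2×0.43)/3 = 0.507, n = (1.200 + 0.496)²/0.0529 = 54.4, so 55 (54.2 by the arcsine formula), against 54 stated. Then 54/0.85 = 63.5, so 64. The plan's figures reproduce; power at 54 versus 108 is about 80%.

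**2. Splitting the response rate.** The plan's chain is 0.65 × (1 − 0.18 − 0.16) = 0.65 × 0.66 = 0.429. Read 0.65 as induction and 0.66 as maintenance. This is an approximation, since 0.65 is a 6-month figure. A quiet subject on monotherapy then responds with probability 0.66.

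**3. Where the combination's gain lies.** The documents do not say.

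- *Equal ratio:* √(0.66/0.429) = 1.240, so induction is 0.806 and maintenance 0.819.
- *All in induction:* induction must be 0.66/0.66 = 1.00, a limiting case.
- *All in maintenance:* maintenance would be 0.66/0.65 = 1.015, which is impossible.

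**4. Mixing in a quiet share q** (assumed; no figure is given). Monotherapy rate = (1−q)×0.429 + q×0.66. Combination rate = (1−q)×0.66 + q×(combination maintenance). Power is by the normal approximation, two-sided 0.05.

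| q | Monotherapy | Combination, equal split | Difference | Power 54 v 108 | Power 64 v 128 |
|---|---|---|---|---|---|
| 20% | 0.475 | 0.692 | 0.217 | 75% | 82% |
| 30% | 0.498 | 0.708 | 0.209 | 73% | 80% |
| 40% | 0.521 | 0.724 | 0.202 | 70% | 78% |

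In the limiting case of all gain in induction, the combination rate stays at 0.66, the difference is 0.185, 0.162 and 0.139, and power at 54 versus 108 is about 61%, 50% and 39%.

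**5. Week-16 outcome.** The difference is (1−q)×(difference in active subjects) + q×(difference in quiet subjects). If quiet subjects show no difference by week 16, it shrinks to 80%, 70% or 60% of its value in active subjects. It shrinks less if the arms differ in flares during the taper.

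**6. Chance imbalance.** The SD of the difference in quiet share between 64 and 128 subjects is √(q(1−q)(1/64 + 1/128)) = 6.1, 7.0 and 7.5 points for q = 20%, 30% and 40%. Multiplied by the monotherapy gap 0.66 − 0.429 = 0.231, one SD moves the crude difference by 1.4, 1.6 and 1.7 points.

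**7. What a stratum buys.** I simulated 40,000 trials with the equal split and q = 30%, leaving out location. Adding baseline activity as a Mantel-Haenszel stratum raised power from 73.1% to 74.4% at 54 versus 108, and from 79.6% to 81.2% at 64 versus 128.

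**The case against.** The case for the plan is substantial. The hypothesis covers maintaining as well as inducing, and one entry route is chronic disease needing a glucocorticoid-sparing drug. A subject held quiet on glucocorticoids is a legitimate candidate there, and a look-back window suits that route. Such a subject is not a guaranteed responder: the taper, the safety and visit conditions, 52 weeks without loss of resolution and the final steroid limits all remain. Quiet subjects can therefore still separate the arms, even before week 16. Table 5 is a registry-style summary that shortens every criterion, Table 2 presents only the main criteria, and the article does not say how a subject with nothing to resolve is coded. All of this stands.

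A reader might infer more than the documents support:

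- *That the 180-day rule contradicts the hypothesis, or that the tables define two competing trials.* The rule is in tension with the induction half only, and Table 5 is an inconsistent abbreviation.
- *That the primary comparison is biased.* Randomisation balances the quiet share in expectation. Chance imbalance is already within the test's error rate, and omitting a prognostic factor from the strata is not in itself an error.
- *That power collapses to 61%, 50% or 39%.* That needs an assumed quiet share and certain induction on the combination.

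What remains is that quiet subjects can enter, the wording differs between tables, and a recorded and probably prognostic factor goes unused.

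**Conclusion.** The point holds as a should-fix. Subjects without inflammation at baseline are eligible under Settings and eligibility. On the natural reading of the outcome, they pass its resolution part without induction. The induction contrast is diluted, most directly at week 16, and chance imbalance in baseline activity goes uncorrected. Validity between arms is not threatened.

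The loss of power cannot be computed from the documents. With 20% to 40% quiet and the gain split equally, the planned 80% at 54 versus 108 becomes about 75% to 70%. With all 64 versus 128 subjects analysed at these rates, it is about 82% to 78%. Both ranges rest on the assumed quiet share, the equal split, and reading the plan's 65% and 66% as induction and maintenance. That baseline activity is strongly prognostic is a judgement; the documents give no estimate. Whether activity at entry should be required is a design trade-off on which the documents do not force an answer.

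**What to change.** - Keep every randomised subject in the primary and week-16 analyses.
- Add presence of any listed inflammatory sign at the baseline exam (yes/no) as a second stratum, with uveitis location, in the Mantel-Haenszel tests of Good Clinical Response and of the week-16 outcome, both overall and pairwise.
- Report both outcomes by baseline activity, with the week-16 result in subjects active at baseline as a supportive analysis.
- State how a subject with no sign at baseline is coded on the resolution part of each outcome.
- Make Tables 2 and 5 state the same activity criterion.

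The eye examinations and OCT at screening or baseline already supply the stratum, so the cost is wording: four strata instead of two, fixed before unblinding. The gain is modest, about 1 to 2 points of power at 30% quiet, plus correction for chance imbalance. Requiring activity at entry would need an amendment and could slow recruitment, and restricting the week-16 analysis to active subjects would discard randomised patients. Neither is needed for this repair.

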### Recruitment

It will extend over 18 months. The participating study sites attends several 10s of new patients every year, with several hundreds or thousands being followed-up, and many of these sites act as reference centres for other secondary and tertiary hospitals. Candidate subjects will be identified from patients lists AND/OR research databases AND among the new patients attended at the sites.

Subject will not receive any financial compensation for participating in the study.

To ensure subject’s retention during follow-up, we will request contact details, carry out reminder phone calls/send emails, review barriers to attend appointments, and educate them in the significance of research follow-up even if they decide to discontinue the study drugs.

### Intervention

All subjects entering the study will be centrally randomised at the baseline visit into one of three study arms, in a 1:1:1 ratio:

*Arm 1* will receive at the baseline visit ADA 80 mg SC loading dose followed a week later by 40 mg every-other-week starting at week 1. They will also receive MTX oral at the baseline visit, with initial dose of 15 mg/week, increasing up to 25 mg/week.

*Arm 2*: MTX with the same schedule as in arm 1.

*Arm 3*: ADA with the same schedule as in arm 1.

In addition to the study drugs, topical adjunctive eye medication will be allowed according to standard practice (intraocular pressure-lowering medication, cycloplegic agents, artificial tears, topical non-steroidal anti-inflammatory drugs…). The use of any biologic therapies with a potential therapeutic impact in NIUs, live vaccines, any other ISD besides the study drugs, intraocular GCs implants or intraocular surgery will be prohibited for the duration of the trial.

To ensure a balance of patients across treatment groups and uveitis anatomic locations, patients will be stratified according to the main site of ocular inflammation (intermediate, OR posterior/panuveitis). Randomisation will not be stratified by site due to the small-expected number of subjects per site.

Block randomisation will ensure that an equal number of patients are randomised to each study arm.

The allocation sequence will consist of a computer-generated random number list generated and held in the Clinical Research Unit of Hospital Clínico San Carlos, hidden from participating Investigators. The allocation sequence will be computer-generated, and it will be implemented through the electronic case report form (eCRF; REDCap), which will assign the treatment group. Study data will be collected and managed using REDCap electronic data capture tools hosted at The Health Research Institute of the Hospital Clínico San Carlos.^62 63^ REDCap (Research Electronic Data Capture) is a secure, web-based software platform designed to support data capture for research studies, providing (1) an intuitive interface for validated data capture; (2) audit trails for tracking data manipulation and export procedures; (3) automated export procedures for seamless data downloads to common statistical packages and (4) procedures for data integration and interoperability with external sources. After obtaining the informed consent for enrolment and confirming that all eligibility requirements have been met, the Unmasked Investigator (see next section) will log into the eCRF and perform the randomisation. Unmasked investigators will then give their assigned treatment to the subjects.

